**2) Objectives Of the study**

Desvenlafaxine is the main active metabolite of Venlafaxine, and has fewer side effects and drug interactions than Venlafaxine. In previous studies, desvenlafaxine 100 mg had no effect on CYP2D6 metabolism and no pharmacokinetic drug interactions with tamoxifen [3].

Desvenlafaxine has been shown to reduce the frequency and severity of hot flashes in several randomized controlled clinical trials in postmenopausal women [4]. In these studies, desvenlafaxine, starting at 50 mg and titrating up to 100 mg, was effective in improving menopausal hot flashes by 55-69%, was safe, and had few side effects. Therefore, desvenlafaxine can be considered an effective and safe treatment for hot flashes in patients with breast cancer taking tamoxifen. Presently, no clinical trials have been conducted as in this study in desvenlafaxine.

This was a 4-week, multi-centre, randomized, double-blind, placebo-controlled study of desvenlafaxine 50 mg and 100 mg to determine whether it is effective in reducing the number and severity of hot flashes in breast cancer patients taking tamoxifen.

1. **Investigational drugs**

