**2) Placebo**

- Starchy tablet, identical in appearance to *Pristiq*

1. **Inclusion criteria, exclusion criteria, number of study participants targeted and rationale for calculation**
2. **Inclusion criteria**

- Women, age 19 years or older
- Diagnosed with atypical ductal hyperplasia, ductal carcinoma in situ, lobular carcinoma in situ, or invasive breast adenocarcinoma stages I through IV.
- Taking tamoxifen regularly (6+ times/week) following the termination of surgery, chemotherapy, and/or radiation therapy due to breast cancer
- Moderate to severe hot flashes occurring 14+ times/week (on average, 2+ times/day) lasting for more than a month.

1. **Exclusion Criteria**

- Pregnant or breastfeeding
- History of seizure or hepatic/renal dysfunction
- Receiving any hormone therapy (including estrogen-/progesterone-/androgens-containing agents) or taking corticosteroids
- Use of antidepressants such as gabapentin, pregabalin, or clonidine to address depression and/or hot flash symptoms.
- Currently suffering from or having a history of severe psychiatric symptoms, such as hallucinations and delusions, mania, and high suicide risk

1. **Number of participants targeted and rationale for calculation**

This study aimed to determine whether the use of desvenlafaxine in patients suffering from hot flashes reduces its symptoms.

The primary endpoint was defined as the percentage reduction in hot flush symptoms = (symptom score at week 4–symptom score at a week before treatment) / symptom score at a week before treatment), and the following assumptions were made to calculate the number of participants to fulfil the primary outcome of the study.

① Level of significance, α = 0.025

The study was divided into three groups (50 mg, 100 mg, placebo), and a type 1 error was defined as 0.025 to determine whether there was a significant difference between the Desvena 50 mg treatment group vs. the placebo group and the 100 mg treatment group vs. placebo group.

② Type II error (β) is set to 0.20, and the power of the test is maintained at 80%.

③ The hypotheses in this study are as follows (two-tailed test):

- Null hypothesis: There is no difference in the rate of reduction of hot flashes between the 50 mg vs. placebo groups or between the 100 mg vs. placebo groups.
- Alternative hypothesis: There is a difference in the rate of reduction of hot flashes between the 50 mg versus placebo or 100 mg versus placebo groups.

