The number of participants was calculated based on a comparison of the desvenlafaxine 100 mg group with the placebo group. In a similar study conducted previously on menopausal women complaining of hot flashes, the mean reduction rate was 0.8 and standard deviation (SD) 0.72 when desvenlafaxine 100 mg was administered, and in the case of the placebo group, the average reduction rate was 0.47 and standard deviation 0.79 [5]. The number of participants in the study that achieved 80% power at a 2.5% significance level was 101 in each arm, for a total of 303. The number of participants was planned to be 339 to account for a dropout rate of 10 %.

1. **Study participant recruitment plan**

Participants will be recruited by posting the [Notice of Recruitment of Research Subjects] in the outpatient departments of the haematology oncology and integrated care center, surgery, obstetrics/gynecology, and mental health clinic. In addition, participants will be recruited by posting a recruitment announcement on “https://cafe.naver.com/uvacenter/158559", the representative internet community of the Breast Cancer Patients' Association.

The principal investigator and funding agency will not exclude patients from participation in this study based on race or socioeconomic status. If the selection criteria for this study were met, every effort will be made to allow as many patients as possible to participate in this study.

1. **Study methods**
2. **Specific research methods**

|  | Baseline | Medication Period | | End of Medication | Tapering period |
| --- | --- | --- | --- | --- | --- |
| Period | T0 | T1 | T2 | T3 | 3days |
| Week | -1w | 0w | 1w | 4w | 4w + 3days |
| Day |  | 1 | 8 | 29 | 29–31 |
| Permissible range of visits |  | ±3 days | ±3 days | ±3 days |  |
| Informed consent | O |  |  |  |  |
| Randomization |  | O |  |  |  |
| Study Drug Administration |  | O | O |  |  |
| Medical record check | O |  |  |  |  |
| Physical Examination |  | O | O | O |  |
| Hot flashes diary | O | O | O | X |  |
| Self-reported questionnaires | O | O | O | O |  |
| Blood/urine tests |  | O |  | O |  |
| Assessment of adverse events |  | O | O | O |  |
| Medication adherence evaluation |  |  | O | O |  |
| Concomitant medication check | O | O | O | O |  |

This was a 4-week dosing, multicenter, randomized, double-blind, placebo-controlled trial.

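### The 100 mg sample-size input (mean 0.80, SD 0.72) is highly implausible for a reduction capped at 1.0, so the stated 80% power is not shown to apply to the primary endpoint

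*Protocol*

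**What the plan says.** Under the heading on the number of participants and its rationale, the Protocol sets the outcome: "The primary endpoint was defined as the percentage reduction in hot flush symptoms". The formula divides the change from the pre-treatment week to week 4 by the pre-treatment score. The Trial Overview builds that score from daily frequency times severity, averaged over a week.

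The same section fixes the test: "Level of significance, α = 0.025" for each comparison with placebo, two-tailed, with 80% power. It then takes its inputs from one earlier study in menopausal women (reference 5): "the mean reduction rate was 0.8 and standard deviation (SD) 0.72 when desvenlafaxine 100 mg was administered", and 0.47 with SD 0.79 on placebo. The sample size that "achieved 80% power at a 2.5% significance level was 101 in each arm" follows, 303 in total, raised to 339 for 10% dropout. The section does not say which outcome, scale or time point the four figures describe.

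The section on the objectives of the study says, from reference 4, that desvenlafaxine titrated from 50 mg to 100 mg "was effective in improving menopausal hot flashes by 55-69" per cent.

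**The concern.** A reduction expressed as a fraction of baseline has a hard ceiling: a woman whose hot flashes disappear scores 1.0, and nobody can score more. A mean of 0.80 leaves only 0.20 above it. A large SD can then come only from a long tail of women who get much worse, which sits oddly with an average reduction of 80%. The 0.80 is also higher than any figure in the range that the protocol quotes when it argues that the drug works.

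These four numbers carry the only power statement in the protocol and the whole case for enrolling 339 women. If they do not describe the percentage reduction in hot-flash score, then 101 per arm and 80% tell the reader nothing about the primary test. The protocol itself fixes the sample size, so this is not a matter left to a statistical analysis plan.

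**Working it through.** **Inputs (Protocol, number of participants and its rationale).** Means 0.80 and 0.47; SDs 0.72 and 0.79; alpha 0.025, two-sided, per comparison; power 80%; dropout 10%. Allocation is 1:1:1 (randomization section). I count a reduction as positive. The printed formula gives the opposite sign, which does not affect this check.

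**1. Reproduce the plan's figure.**
- Difference: 0.80 − 0.47 = 0.33.
- Combined SD: √((0.72² + 0.79²)/2) = √(1.1425/2) = 0.756.
- Normal approximation: n = (2.2414 + 0.8416)² × 1.1425 / 0.33² = 99.7, so 100 per arm.
- Noncentral t: power is 79.6% at 100 and 80.0% at 101 per arm.
- Dropout: 101/0.90 = 112.2, so 113 per arm; 3 × 113 = 339.

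The stated 101, 303 and 339 all reproduce.

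**2. Test the inputs against the endpoint's scale.** For a variable with upper limit 1, lower limit L and mean m, the largest possible SD is √((1 − m)(m − L)). Setting this equal to the stated SD s gives the least extreme lower limit that can produce it: L = m − s²/(1 − m).

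| | 100 mg (0.80, SD 0.72) | Placebo (0.47, SD 0.79) |
|---|---|---|
| Largest SD if nobody worsens (L = 0) | √(0.20 × 0.80) = 0.40 | √(0.53 × 0.47) = 0.50 |
| Largest SD if nobody more than doubles her score (L = −1) | √(0.20 × 1.80) = 0.60 | √(0.53 × 1.47) = 0.88 |
| L needed for the stated SD | 0.80 − 0.5184/0.20 = −1.79 | 0.47 − 0.6241/0.53 = −0.71 |
| Week-4 score at that L | 2.79 × baseline | 1.71 × baseline |

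In the 100 mg arm some women must therefore finish at 2.79 times baseline or worse. In the limiting case 0.20/2.79 = 7% of the arm are at that value and all the others are completely free of hot flashes. The placebo pair is less strained: it needs some women to worsen by about 71% or more.

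**3. Compare with the objectives section.** The top of the cited range is 0.69, and 0.80 − 0.69 = 0.11. The assumed mean lies 11 percentage points above it, without explanation.

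**4. What 101 per arm would give on a tighter scale.** The documents give no SD known to belong to this endpoint, so I assume 0.35 to 0.50. Detectable difference at 80% power = 3.083 × SD × √(2/101) = 0.434 × SD.
- SD 0.35: 0.15.
- SD 0.50: 0.22.

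**5. Direction of the error.** Keep the means and take the largest SDs possible if nobody worsens (0.40 and 0.50, combined 0.452): power is 99.8%. If instead the true difference is below 0.15, power is under 80% even at SD 0.35. The documents do not settle which case is nearer.

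**The case against.** The strongest reply is that nothing here is impossible. Worsening has no limit, so both pairs of mean and SD can occur. A heavily skewed outcome can produce the 100 mg pair: if the week-4 to baseline ratio were lognormal with mean 0.20 and SD 0.72, only 3.6% of women would worsen and 1.3% would more than double. That stands, and it rules out saying that the figures cannot be percentage reductions. But the same model puts the median reduction at 95%, which makes the input no easier to believe.

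A reader might go further in four ways that the documents do not support.

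- *That 0.80 contradicts 55-69%.* The two come from different citations, and neither outcome is defined. If the range were for frequency alone, a frequency-times-severity score could fall further: 69% fewer flashes with an assumed 35% lower severity gives 1 − 0.31 × 0.65 = 0.80. The figures are unreconciled, not contradictory.
- *That the inputs are on another scale.* The section calls them a reduction rate, the same idea as in its hypotheses. Another scale is one explanation, but only the cited study can show it.
- *That a normal distribution with these values, which puts 39% of the 100 mg arm above 1.0, invalidates the calculation.* It shows that individual values would not be normal. A comparison of means with 101 per arm does not need them to be.
- *That true power is 43% (active mean 0.69) or 7% (0.55).* Those figures set one source's active mean against another's placebo mean, and keep the very SD in dispute.

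**Conclusion.** The point holds as a fault in the assumptions, not in the arithmetic. The 100 mg input is highly implausible on the scale of the primary endpoint: its SD of 0.72 compares with a maximum of 0.40 without any worsening and 0.60 without anyone more than doubling her score. The placebo input is strained much less. Because the protocol names neither the outcome, the scale nor the time point of the source figures, and does not reconcile 0.80 with its own 55-69%, the 80% power is not shown to apply to the primary comparison.

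The size of any error, and its direction, cannot be fixed from the document. The detectable difference of about 0.15 to 0.22 is an illustration that rests on the assumed SDs of 0.35 to 0.50. The limits on the SD rest only on the ceiling of 1.0, which follows from the endpoint's definition.

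**What to change.** - Check in the cited study which outcome, scale and time point the four figures refer to, and state this in the sample-size section.
- If they are not percentage reductions in hot-flash score, replace them with a mean and SD on that scale. If they are, say so and comment on the spread.
- Explain how the assumed 100 mg mean relates to the 55-69% in the objectives section.
- Restate the power, or the detectable difference, that 101 evaluable women per arm provide at two-sided 0.025.

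The cost is a look at the source and a rewritten paragraph. The restatement itself adds no patients. The stated power may become less favourable, and whether 339 is still a comfortable number can be judged only once the inputs are confirmed.

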| Trial Design | # 4-week dosing, multicenter, randomized, double-blind, placebo-controlled study  # Arm 1: Desvenlafaxine 100mg group  First week: one tablet of desvenlafaxine 50mg every morning.  Next three weeks: Two tablets of desvenlafaxine 50mg every morning.  Subsequent three days: One tablet of desvenlafaxine 50mg every morning for gradual tapering  # Arm 2: Desvenlafaxine 50mg group  First week: one tablet of desvenlafaxine 50mg every morning.  Next three weeks: One tablet of desvenlafaxine 50mg plus one placebo tablet every morning.  Subsequent three days: One placebo tablet every morning for gradual tapering.  # Arm 3: Placebo group  First week: one placebo tablet every morning.  Next three weeks: Two placebo tablets every morning.  Subsequent three days: One placebo tablet every morning  # During the study period, participants are required to maintain a daily diary recording their hot flashes symptoms. They will also visit the hospital a total of four times, undergoing four questionnaire assessments and two sets of blood and urine tests.  # Survey Questionnaires  - CGI (Clinical Global Impression), adverse event assessment.  - Hot flashes diary (completed daily)  - EORTC-QLQ-CIPN-20 (peripheral neuropathy).  - MINI (screening for psychiatric disorders)  - PHQ-9 (depression), GAD-7 (anxiety), MDQ (mania)  - PSQI (sleep quality)  - MEQ (morningness-eveningness preference)  - MCTQ (circadian rhythm misalignment)  - FACIT-Fatigue (fatigue)  - FACT-B (quality of life)  - BMQ (Medication Belief Scale), BIPQ (Illness Perception Questionnaire).  - MSPSS (Multidimensional Scale of Perceived Social Support)  - BIS (Body Image Scale)  - CDRS (Connor-Davidson Resilience Scale)  # Blood and urine tests  a) Female sex hormones  - Estrogen, estradiol, progestron, lutenizing hormone (LH), follicle-stimulating hormone (FSH), AMH (Anti-Müllerian hormone)  b) Monoamine metabolites & serotonin receptor  - 5-hydroxyindole acetic acid (5-HIAA), 3-methoxy-4-hydroxyphenylglycol (MHPG)  - Platelet 5HT2A receptor  c) Pro & anti-inflammatory cytokines  - Interleukin-1β (IL-1β), IL-6, IL-12, and IL-18, tumor necrosis factor alpha (TNF-α),  - interferon gamma (IFNγ), granulocyte-macrophage colony stimulating factor (GM-CSF)  - IL-4, IL-10, IL-11, IL-13  d) KNDy peptides  - Kisspeptin, neurokinin B, dynorphin  e) Calcitonin gene‐related peptide (CGRP)  f) Serum lipid profile, Urinalysis  g) genetic polymorphism in estrogen receptors (ESR1 PvuII; rs#2234693 and XbaI; rs#9340799 and ESR2-02; rs#4986938) and serotonin transporter gene (SLC6A4; rs#11080121)  h) Urinalysis |

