Participants will be randomized to receive desvenlafaxine or placebo for a total of 4 weeks + 3 days, maintain a daily hot flashes diary, and have a total of 4 clinic visits for four questionnaire assessments and two blood and urine tests. Height, weight, BMI, and blood and urine tests will be performed at T1 and T3.

The participants will complete an informed consent form at the initial visit, and an initial questionnaire assessment will be administered. If participants did not know the exact date of menstruation in the menstrual history assessment section and the date of breast cancer diagnosis in the cancer-related information section, the following are written: if participants remember only the month, write 15 days (e.g., October ?day 2017 -> October 15, 2017), and if participants remember the beginning, middle, and end of the month instead of the exact date, write 5, 15, and 25 days, respectively (e.g., early October 2017 -> October 05, 2017).

Afterwards, the participants are advised to maintain a hot flashes diary without medication for one week to assess the baseline status before medication. During the same period, patients will be randomized into the desvenlafaxine 100 mg, 50 mg, or placebo group by a third-party institution unrelated to the study (Medical Research Collaborating Center).

From one week after study registration, each of the three groups will be administered a dose of desvenlafaxine or placebo for four weeks. To reduce the adverse effects of abrupt discontinuation in the desvenlafaxine 100 mg group, there will be a 3-day tapering period with one tablet of desvenlafaxine 50 mg or one tablet of placebo.

During the administration period, the patients will complete a hot flashes diary and medication compliance assessments. After participating in the study, patients will receive a hot flashes diary form to record for 1 week, 1 week, and 3 weeks, at visits of -1, 0, and 1 week, and the data written by the patient during that period will be included in the case report form of the previous periods. During the above visits, a physical examination and assessment for adverse events and medication adherence will be performed.

Self-reported questionnaire assessments will be administered at visits 1 week prior to study enrollment and 0, 1, and 4 weeks after study enrolment. Moreover, blood and urine tests will be performed at 0 and 4 weeks after study enrollment.

1. **Control group setting and randomization method**

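### Adverse events are last assessed at T3, nominally the first taper day, so reactions to stopping the drug are not systematically captured and what is seen differs by arm

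*Protocol*

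**What the plan says.** - **Assessment times.** The schedule table in the protocol (Study methods, Specific research methods) has this adverse-event row: "Assessment of adverse events | | O | O | O". The marks fall under T1 (day 1), T2 (day 8) and T3 (day 29). The table's column order is "Period | T0 | T1 | T2 | T3 | 3days", so the taper has its own column, days 29–31, and no assessment is marked in it.
- **Visit window.** "Permissible range of visits | | ±3 days | ±3 days | ±3 days". No window is given for the taper.
- **Visits.** The text below the table says that participants will "have a total of 4 clinic visits for four questionnaire assessments and two blood and urine tests". These are T0 to T3. The hot flash diary forms cover 1, 1 and 3 weeks from week −1, so the diary also ends at week 4.
- **Duration of tablets.** "Participants will be randomized to receive desvenlafaxine or placebo for a total of 4 weeks + 3 days".
- **Purpose of the taper.** "To reduce the adverse effects of abrupt discontinuation in the desvenlafaxine 100 mg group, there will be a 3-day tapering period". The sentence goes on to allow either one 50 mg tablet or one placebo tablet on those days.
- **Tablets on the last three days** (Trial Overview, Trial Design). For the 100 mg arm: "Subsequent three days: One tablet of desvenlafaxine 50mg every morning for gradual tapering". For the 50 mg arm: "Subsequent three days: One placebo tablet every morning for gradual tapering". The placebo arm also takes one placebo tablet, without the tapering description.
- **Role of safety.** The Trial Overview includes safety in the research aim and lists adverse events first under safety evaluation.

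**The concern.** The protocol recognises a specific drug risk, adds three days of tablets to reduce it, and then schedules no measurement of it. The nominal last assessment falls on the day the taper begins, while the 100 mg arm still has active tablets to take.

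The safety half of the trial's aim is at stake. Events on stopping active drug can occur only in the two active arms. If collection ends before or around the moment of stopping, the omission is one-sided and the comparison with placebo can look more favourable than it should. No analysis plan can repair this later, because events that were not collected cannot be tabulated.

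A smaller matter concerns the 50 mg arm. Its last three days are placebo but are described as a taper, while the stated reason for the taper names the 100 mg group only.

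**Working it through.** **1. The plan's own day count.** Four weeks from day 1 is 4 × 7 = 28, so main dosing is days 1–28. Three taper days follow: 28 + 1 = 29 to 28 + 3 = 31. This matches the table. The T3 window is 29 − 3 = 26 to 29 + 3 = 32.

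**2. Last active tablet by arm** (from Trial Design). In the 50 mg arm active drug ends with week 4, on day 28. In the 100 mg arm it ends with the taper, on day 31.

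**3. What a T3 visit on day v can see.** Full days without active drug completed before the visit day are v − 29 in the 50 mg arm and v − 32 in the 100 mg arm, where positive. This assumes that day 1 is the first tablet and that the taper days are fixed as in the table.

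| T3 on day | 50 mg arm | 100 mg arm |
| --- | --- | --- |
| 26–28 | still on active drug | still at full dose |
| 29 (nominal) | first day off, 0 full days | first step-down day |
| 30 | 1 full day off | second step-down day |
| 31 | 2 full days off | last active tablet |
| 32 | 3 full days off | first day off, 0 full days |

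Of the seven permitted days, three (30–32) follow at least one full day off active drug in the 50 mg arm. None does in the 100 mg arm, where only day 32 comes after the last active tablet at all. Days 30–32 could also show early effects of the step-down itself in the 100 mg arm.

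**4. The other reading of the schedule.** If the taper starts only after the T3 visit, whenever that visit takes place, no assessment follows the end of main dosing in either arm.

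**5. How many participants are concerned.** The section on the number of participants gives 101 per arm, 303 in total, and 339 after a 10% dropout allowance. This reproduces: 101 / (1 − 0.10) = 112.2, rounded up to 113, and 3 × 113 = 339. Those enrolled in the two active arms number 2 × 113 = 226. Those expected to reach the end of dosing number 2 × 101 = 202. The second figure applies here, because participants who drop out earlier do not stop in this period.

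**6. How many events.** The documents give no rate of stopping reactions, so no count of missed events can be derived.

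**The case against.** Four objections deserve an answer.

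*The window.* A reader might infer that stopping reactions are never captured. The documents do not support that. T3 can be as late as day 32, nominal T3 is itself a taper day, and in the 50 mg arm it is the first day without active drug. Some reactions could be recorded. This objection stands against the word never. It does not rescue the plan, because capture by chance of visit date is unsystematic and, as the table shows, unequal between the arms.

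*The placebo taper tablets.* A reader might infer that the placebo tablets in the 50 mg arm cause the gap, or that the two sections contradict each other on what is given. Neither holds. Tablet content does not determine when events are assessed. The full sentence in Specific research methods allows a placebo tablet, which agrees with Trial Design, and one matching tablet in every arm suits a double-blind design. Only the description of the 50 mg arm's placebo days as tapering is loose.

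*Scope.* The comparison over the four weeks of main dosing is unaffected, as are the primary endpoint and the sample size. Comparing stopping reactions between the two doses is not a stated aim. All of this stands, and it limits the weight of the point. It does not remove it, since safety is part of the aim and tablets are still being taken after nominal T3.

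*Text not supplied.* The protocol text at hand ends with the randomization section, which covers only withdrawal and unblinding after a serious reaction. A later safety section might provide for reports after T3. That cannot be excluded, so the claim is that no later contact is shown. The blank taper column would need filling in any case.

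**Conclusion.** The point holds as a gap in safety data collection. Followed as written, the protocol has no systematic capture of adverse events during the taper and after the last tablet. What is captured depends on where T3 falls within days 26–32 and favours the 50 mg arm for detection: up to 3 full days off active drug, against none in the 100 mg arm. Adverse events in the active arms can therefore be understated. Whether they will be, and by how many, cannot be said.

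About 202 participants come off active drug in this period. That figure rests on the protocol's own 10% dropout allowance. The arm-by-arm timing rests on the taper days being fixed at 29–31. If they instead follow the T3 visit, the gap is complete in both active arms.

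The change should be made because it is cheap and the missing data cannot be recovered afterwards. It has no bearing on the efficacy result.

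**What to change.** 1. Fill the taper column of the schedule. Extend adverse-event collection through the three taper days and the days just after the last tablet, with one extra diary page closed by one short telephone contact. Do this identically in all three arms so that blinding is kept.
2. State whether the taper days are fixed in calendar terms or begin at the T3 visit.
3. Tabulate these events by arm as a separate period, apart from the four weeks of main dosing.
4. Reconcile the description of the 50 mg arm's last three days in Trial Design with Specific research methods, which gives the purpose of the taper for the 100 mg group only. No dose or taper rule is proposed here.

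The cost is one page and one call per participant by existing staff, at most 339 calls, plus a change to the protocol wording. No clinic visit is added and the sample size does not change.

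### The T3 visit shares Day 29 with the first taper day and may run to Day 32, so T3 samples and questionnaires can be taken at reduced or no active dose

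*Protocol*

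**What the plan says.** **Dosing (Protocol, Trial Overview, Trial Design row).** Tablets are taken every morning, for one week and then for three more. For the 50 mg arm the last three of these weeks read "Next three weeks: One tablet of desvenlafaxine 50mg plus one placebo tablet every morning", followed by "Subsequent three days: One placebo tablet every morning for gradual tapering". For the 100 mg arm the taper reads "Subsequent three days: One tablet of desvenlafaxine 50mg every morning for gradual tapering". The placebo arm takes placebo throughout.

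**Visits (Protocol, Specific research methods, schedule table).** T3, the end-of-medication visit, is on Day 29. The taper column covers Days 29 to 31. The window row reads "Permissible range of visits | | ±3 days | ±3 days | ±3 days". Questionnaires are marked at all four visits ("Self-reported questionnaires | O | O | O | O"). No diary form is issued at T3 ("Hot flashes diary | O | O | O | X").

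**Sampling (text below that table).** "Height, weight, BMI, and blood and urine tests will be performed at T1 and T3", and again by week: "blood and urine tests will be performed at 0 and 4 weeks after study enrollment".

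The protocol does not say that T3 must come before the first taper tablet, at what point of the day the sample is drawn, or that a late T3 visit postpones the taper.

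**The concern.** T3 is meant to describe four weeks of treatment with 100 mg, 50 mg or placebo. Its nominal day is already the first taper day, and its window extends past the last one. A woman who attends late but within the window is assessed on a different regimen from the one to which her result will be attributed.

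The departure is not the same in each arm. It is nil for placebo, a step down for 100 mg and a complete stop of active drug for 50 mg. Randomisation does not balance it, and it depends on when each woman attends. The protocol itself treats stopping effects as real, since it adds the taper to soften abrupt discontinuation in the 100 mg arm.

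At stake are the T3 measures taken once, at the visit. They include monoamine metabolites, the platelet serotonin receptor and other blood markers, and the mood, sleep and fatigue questionnaires. Blood and urine are collected only at T1 and T3, so no other on-treatment sample can stand in for T3.

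**Working it through.** The plan gives no figure on this point to reproduce. The check is a day count, with T1 as Day 1 and dosing from Day 1.

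**Inputs.** Treatment of 1 + 3 weeks, a three-day taper and its content by arm (Trial Overview); T3 on Day 29, taper on Days 29 to 31, T3 window of 3 days either side (schedule table).

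**Step 1, treatment days.** 7 + 21 = 28, so the last full-dose tablet is on Day 28. The three following days are 29, 30 and 31, which agrees with the schedule table.

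**Step 2, permitted T3 days.** 29 − 3 = 26 to 29 + 3 = 32, which is 7 days.

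**Step 3, active intake (mg) in the 100 mg / 50 mg / placebo arms.**

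| T3 day | That morning | Day before | Full-dose contrast kept? |
|---|---|---|---|
| 26 | 100/50/0 | 100/50/0 | yes |
| 27 | 100/50/0 | 100/50/0 | yes |
| 28 | 100/50/0 | 100/50/0 | yes |
| 29 | 50/0/0 | 100/50/0 | only if assessed before the morning tablet |
| 30 | 50/0/0 | 50/0/0 | no |
| 31 | 50/0/0 | 50/0/0 | no |
| 32 | 0/0/0 | 50/0/0 | no |

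**Step 4, count.** The contrast is kept on 3 of 7 days (26 to 28), lost whatever the hour on 3 of 7 (30 to 32), and undetermined on the nominal day. In the 50 mg arm the last active tablet is on Day 28, so a Day 32 visit is 32 − 28 = 4 days later.

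**Step 5, can a late visit simply delay the taper?** The taper has fixed days in the table. The row for study drug administration is marked at T1 and T2 but not at T3. If that row means dispensing, the taper tablets are already at home by Day 29. Nothing in the text supports a delay.

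**Step 6, both windows.** T1 also has a window of 3 days either side. If both windows are counted from the nominal calendar, T3 can fall anywhere from dosing day 29 − 3 − 3 = 23 to 29 + 3 + 3 = 35. The one-visit count above is the simpler reading and is used here.

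**The case against.** The strongest reply is that the intent is plain. T3 heads the end-of-medication column, which stands before the tapering column, and the text places sampling at four weeks. A Day 29 visit before the morning tablet follows the Day 28 full doses. This stands for Days 26 to 28 and for an early Day 29 visit. It does not cover Days 30 to 32, which the stated window permits.

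It may also be said that the protocol states no between-arm comparison of T3 biomarkers. Its biological aim is to predict risk and treatment response, and its hypotheses concern hot flashes, each dose against placebo. That is correct and limits the importance of the point. It does not remove it, because T3 values are still labelled as four-week values.

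Some stronger readings are tempting, but the document does not support them:

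- **That the T3 contrast is never 100/50/0 mg.** The window includes full-dose days.
- **That 4 of 7 days on or after the first taper day means 4 in 7 women are affected.** This counts calendar days. No distribution of visits is given, and on Day 29 the answer depends on the hour.
- **That the 50 mg versus placebo contrast shrinks or reverses.** This is possible, but no figure supports it. The protocol gives no half-life. A fraction remaining 24 hours after a dose is only the ordinary level before the next daily tablet, so it shows no loss at a Day 29 visit before the tablet. Nor is plasma decay shown to track these markers.
- **That all T3 measures are affected alike.** Genotype does not change with timing. No recall periods are given for the questionnaires, and several, such as chronotype, social support or resilience, are not evident measures of short-term drug effect.
- **That the primary endpoint is compromised.** It uses the week-4 diary score. A late T3 could carry the last diary form into taper days, but that is a different point.

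**Conclusion.** The point holds as a minor one. The schedule lets T3 samples and questionnaires be taken at reduced or no active dose, differently by arm, on 3 of the 7 permitted days regardless of hour, and on Day 29 if they follow the morning tablet. This goes beyond detail that a statistical analysis plan could supply, because the overlap comes from a stated window and stated taper days.

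The count assumes that T1 is Day 1, that dosing follows the stated weeks and that the taper keeps its tabulated days. The size of any bias cannot be derived from the document. It concerns secondary and exploratory T3 measures only. The sample size and the primary test are unchanged.

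**What to change.** Reconcile the Trial Design row, the schedule table and the sampling text, with no change to any dose:

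- State that T3 assessments are timed before the first taper tablet, and resolve the shared Day 29. How visits and tablets are arranged to achieve this is for the sponsor.
- Give T3 a window that does not run into the taper, for example −3/0 days. This leaves Days 26 to 29 (4 days instead of 7), all at full-dose contrast once the order on Day 29 is stated.
- Record the date and time of the last full-dose tablet and of T3 sampling.
- Keep all T3 values in the main analysis and add a sensitivity analysis by whether T3 preceded the taper. Dropping late values would be an exclusion after randomisation, and attendance may itself be related to arm.

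The cost is an edit to the schedule, added case report form fields for these dates and times, a narrower visit window and some visits logged as deviations.
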